#### Strategies to improve adherence to interventions {11c}

The patients themselves do not have to do anything to adhere to the intervention or provide measurements of primary and secondary outcomes. The intervention itself will be administered by the ICU/HAU staff at each center. Strategies to ensure the staff adhere to the experimental procedures include education sessions on the purposes and procedures of the trial before the start of the experiment, and during the trial. The ICU/HAU staff have also been a part of the protocol development to ensure a seamless incorporation of experimental procedures into the standard workflow. The primary and secondary outcomes are already captured as part of the standard of care and will be recorded in patient charts. These charts will be reviewed by the research staff to fill out the study case report forms (CRFs).

#### Relevant concomitant care permitted or prohibited during the trial {11d}

Clinical care will continue as per the discretion of the patient’s healthcare team. The intervention is a CVAD locking fluid that remains only in the lumen of the CVAD; it will never actually enter the patient’s circulation. The locking fluid will be aspirated out of the catheter following the end of locking. As such, there is no potential for drug interactions, and we do not foresee any restrictions in enrolling patients based on other types of concomitant care.

#### Provisions for post-trial care {30}

There is no anticipated harm and compensation for trial participation.

### Outcomes {12}

The following is the primary outcome:Incidence rate of the following: confirmed CLABSI as diagnosed in accordance with the Fraser Health CLABSI diagnosis algorithm (see Additional file 1) based on the NHSN guidelines, CVAD replacement due to occlusion, and/or catheter obstruction requiring alteplase use. The composite incidence rate will be calculated as the number of events divided by the number of catheter days. The patient is considered at risk during the time the patient is in the ICU/HAU and has a catheter placed. Multiple outcomes occurring within a 24-h time frame will be counted as a single event, except for CLABSI; any occurrence less than 2 calendar days following a previous CLABSI and subsequent catheter removal will be considered attributed to the previous catheter, and treated as a single event. The occurrence outcomes will be monitored twice daily via reviewing patient charts and participating with discussions with the patients’ treating nursing staff. Outcomes will be tested for and diagnosed according to clinicians in charge of patient care.

#### Note about the primary outcome

In the case of suspected CLABSI, diagnostic procedures will proceed according to the Fraser Health CLABSI Case Identification Algorithm, in all participating ICU/HAUs. Following CLABSI diagnosis, patients will receive antibiotic treatment as necessary. Should the care team decide that replacement of the CVAD be necessary, treatment will proceed according to the standard of care. Upon subsequent locking procedures, patients will receive the same locking solution as the rest of the hospital unit at that particular point of the study procedure.

The decision to measure CLABSI as an outcome instead of CRBSI was made to keep with the real-world, pragmatic design of the trial. Diagnosis of CRBSI would require specific research-related procurement of samples and microbiological testing that due to the sheer size of the trial, would be too expensive and difficult to implement logistically. Additionally, the use of the CLABSI outcome enables a comparison of rates of catheter-related infections of ICUs participating in this study to those participating in the Canadian Nosocomial Infection Surveillance Program [30]. This surveillance program collects hospital-acquired infection data from 40 participating hospitals across Canada and serves to inform governments and policymakers of the burden of hospital-acquired infections. We chose to also report the same outcome so that the results of our study could be more widely compared to the levels of CLABSI across other Canadian ICUs.

To keep with the current standard of care, CVADs will only be tested for infection at the discretion of the treating physician and will not be tested systematically. This is another factor that we feel justifies the use of CLABSI over CRBSI, although we recognize the outcome is not as rigorous as the CRBSI diagnosis and may be considered a limitation of our work.

#### Secondary outcomes

All outcomes will be assessed twice daily via reviewing the patient charts and participating in discussions with the patients’ treating nursing staff. The outcomes will be tested for and diagnosed according to clinicians in charge of patient care.Incidence rate of confirmed CLABSI (as adjudicated according to the NHSN criteria described previously).Incidence rate of suspected CLABSI. A case of suspected CLABSI will be defined as a case in which no microbiological testing was performed on the suspected catheter or through-catheter blood sample, with the patient having a positive blood culture result of a common bacteria associated with a CVAD infection with no other identifiable source of infection.Incidence rate of catheters requiring removal due to occlusion, as determined by inspecting relevant notes on the patient chart and discussion with the nursing staff.Incidence rate of catheters requiring alteplase use as determined by inspecting relevant notes on the patient chart and discussion with the nursing staff.Incidence rate of catheter-associated venous thrombosis, as determined by inspecting relevant medical imaging and notes on patient charts.Incidence rate of catheter colonization, as diagnosed according to the Clinical Practice guidelines of Infectious Diseases Society of America [31].Classification of types of microorganisms isolated from a convenience sample of removed CVAD’s through culture-dependent and independent techniques.Health economic evaluation of the cost of intervention versus health care utilization and associated costs of diagnosis and treatment of catheter complications

#### Participant timeline {13}

Participant timeline is described in Table 1.

**Table 1 Tab1:** Participant timeline

Procedure	Pre-lock	First lock	During locking period	During ICU/HAU stay
Informed consent	x^a^			
Inclusion/exclusion criteria	x^b^			
Demographics	x			
Medical history	x			
Consent to receive blood products	x^c^			
Pregnancy test	x^d^			
Prior/concomitant medication	x^e^			
Central line placement (as per SOC)	x			
Central line flushing (q12 as per SOC)^f^		x	x	
Central line aspiration^g^		x	x	
Study medication (in the experimental group)		x	x	
Standard of care (in the control group)		x	x	
Adverse events		x	x	
Data collection	x^h^	x^h^	x^h^	x^i^

^a^Informed consent will be collected in a waived fashion

^b^Confirmation of the eligibility will occur at the baseline visit to make sure that the person still remains eligible

^c^The patient must provide consent to receive blood products before moving forward

^d^Pregnancy test, if completed, would need to be negative before going forward

^e^As other medications may have an unforeseen impact on 4% tetrasodium EDTA, these medications are being tracked to determine if this is the case

^f^Standard of care—the central line is periodically flushed with normal saline or citrate (for hemodialysis catheters) to ensure patency

^g^Standard of care—the central line lock is aspirated of any solution that may remain in the lock between locking or medication administration

^h^Data collection, if applicable, will occur during the defined periods when patients are hospitalized in the ICU/HAU. This data will be collected in order to determine primary and secondary outcomes

^i^Data collection in the form of checking of medical imaging reports will continue for the duration of the patients’ ICU/HAU stay, even if the patient no longer has a central line

Participants will be enrolled during the first three-and-a-half months of each four-and-a-half--month period. Each participant will be followed until they leave the ICU/HAU, they reach the end of the 28-day follow-up period, or they die. Data collection for incidence rates of confirmed/suspected CLABSI, catheter occlusion requiring removal, catheter obstruction requiring alteplase use, direct cost related to alteplase use for catheter occlusion, and catheter colonization will continue via the combination of in-person discussion and chart review for the duration of time that the patient has their catheter in place, until they are discharged from the ICU/HAU, or they die, whichever comes first. In the event that a blood culture is taken on either the last day of catheter placement or the last day that the patient is in the unit, the research coordinator will continue to monitor the patient charts for the result of that blood culture, as a bloodstream infection may still be attributed to the catheter.

Data collection in the form of monitoring medical imaging results for the incidence rate of catheter-associated venous thrombosis will continue for the entirety of the patients’ ICU/HAU stay, even if all CVADs have been removed. The senior investigators’ clinical experience indicates that thrombosis from a CVAD in the upper thoracic region is sometimes not discovered until weeks after the CVAD has been removed, as it may take this long for the patient to develop symptoms of thrombosis. As such, the research coordinators will continue to follow the medical imaging results of the patients who are still in the ICU/HAU but have had all central lines removed and are no longer receiving the study intervention.

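### CLABSI collection ends at catheter removal, so a first positive culture drawn the next day in a patient still in the unit is not captured: a small under-count, with no bias between arms shown

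*Protocol article*

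**What the plan says.** The Participant timeline {13} section sets the collection period for confirmed and suspected CLABSI, together with the occlusion, alteplase and colonization outcomes. Collection runs "for the duration of time that the patient has their catheter in place, until they are discharged from the ICU/HAU, or they die", whichever of these comes first. One sentence extends it. If "a blood culture is taken on either the last day of catheter placement or the last day that the patient is in the unit", the coordinator goes on checking the chart for that result, "as a bloodstream infection may still be attributed to the catheter".

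Collection after line removal is otherwise described only for thrombosis. Footnote i of Table 1 continues the check of imaging reports to the end of the unit stay, "even if the patient no longer has a central line".

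The Outcomes {12} section counts "confirmed CLABSI as diagnosed in accordance with the Fraser Health CLABSI diagnosis algorithm" in the primary composite. It defines time at risk as follows: "The patient is considered at risk during the time the patient is in the ICU/HAU and has a catheter placed". It also has a counting rule for repeat infections: "any occurrence less than 2 calendar days following a previous CLABSI and subsequent catheter removal will be considered attributed to the previous catheter", and the two are treated as a single event. The algorithm itself is in Additional file 1, which is not at hand.

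**The concern.** The protocol accepts that an infection may be attributed to a catheter after it has been taken out, but its collection rule does not reach the day after removal. Whether a post-removal culture is followed depends on whether it falls on the day the patient leaves the unit, not on how long the catheter has been out.

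Confirmed CLABSI is one of three components of the primary composite. Confirmed and suspected CLABSI are also separate secondary outcomes. The note on the primary outcome justifies choosing CLABSI partly because the rates can be compared with national surveillance. If the algorithm attributes early post-removal cultures to the removed line, a count that omits them falls below a rate obtained by applying the algorithm in full.

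**Working it through.** The plan gives no figure on this point to reproduce. The first check applies the written rule to each possible culture date.

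Let the last catheter be removed on day D and the patient leave the unit on day E, with no other CVAD in place after D.

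- Culture on D: last catheter day, so its result is followed.
- Culture on D+1, where D+1 is before E: collection has ended and neither exception applies, so it is not collected.
- Culture on any later day before E: not collected.
- Culture on E: last unit day, so on the literal wording its result is followed, whatever the gap between D and E.

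For example, with D = 5 and E = 12, a culture on day 6 is missed, while the result of a culture on day 12 is monitored.

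Three other statements might close the gap, but do not:

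- General follow-up to unit exit, day 28 or death (Participant timeline {13}) is broader, but the sentence specific to CLABSI is narrower and governs.
- Twice-daily assessment (Secondary outcomes) sets frequency, not duration.
- The extension past line removal in Table 1, footnote i, and in the text after the table covers imaging only.

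**Size as a share of CLABSIs.** Neither input is in the documents. Assume a constant daily hazard, one attributable day after removal, mean dwell d of 5 to 10 catheter days, and a fraction r of 0.3 to 0.6 still in the unit the next day. Strictly, r should exclude patients with another line and those leaving that day, since both are already covered.

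Missed share = r / (d + r)

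- Low: 0.3 / (10 + 0.3) = 2.9%
- High: 0.6 / (5 + 0.6) = 10.7%

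**Size as a count.** Take the 1690 patients of Sample size {14}, one catheter each, and the pooled 4.59 CLABSIs per 1000 catheter days quoted in Background and rationale {6a} as the daily hazard.

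- Low: 1690 × 0.3 × 0.00459 = 2.3 missed
- High: 1690 × 0.6 × 0.00459 = 4.7 missed

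The planning risks of 20% and 14% imply 845 × 0.20 + 845 × 0.14 = 287 patients with the composite, so 2.3 to 4.7 is about 0.8% to 1.6% of that number.

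**Wider bracket.** Assume instead 4 to 10 catheter days per patient and 5% to 20% of CLABSIs first cultured after removal.

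- Total CLABSIs: 1690 × 4 × 0.00459 = 31 to 1690 × 10 × 0.00459 = 78
- Missed: 31.0 × 0.05 = 1.6 to 77.6 × 0.20 = 15.5, or about 0.5% to 5% of 287

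**Direction.** The outcome is events per catheter day. With hazard h and dwell d, the events captured under the current rule are h × d over d days, so the captured rate is h × d / d = h for any dwell. A difference in dwell between arms therefore does not bias the captured rate under this model.

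**The case against.** The strongest reply is that attribution is settled by the diagnosis algorithm in Additional file 1, so the protocol text alone cannot show that a first culture on the day after removal is countable. That stands, and it is why the window must be taken from that file. It does not remove the gap, because a culture that is never collected cannot be put through the algorithm.

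A reader might infer three stronger points. The documents do not support them.

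- **That the 2-calendar-day rule in Outcomes {12} fixes the window being missed.** It merges a repeat occurrence with a previous CLABSI. It shows that attribution to a removed catheter is contemplated, but sets no window for a first infection.
- **That a culture taken long after removal, on the last unit day, enters the numerator.** The text only has its result monitored, and attribution must still pass the algorithm. The exception is more naturally read as covering patients who leave with a line in place, a situation described in section {18b} on retention and follow-up. The wording does not say so, and that is all that can be held against it.
- **That the rule biases the comparison against EDTA because longer dwell loses fewer events.** The captured rate per catheter day does not depend on dwell under the constant-hazard model. The suggested mechanisms are also weak: after a replacement for occlusion a catheter is still in place, so collection continues, and a culture drawn up to or on the removal day is already captured.

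**Conclusion.** The point holds as a gap in ascertainment. Followed as written, the protocol does not collect a first positive culture drawn the day after removal of the last line in a patient who stays in the unit, and the last-unit-day exception leaves the catheter requirement unstated.

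The likely consequence is a small under-count of about 3% to 11% of CLABSIs. That range rests entirely on the assumed dwell and length of stay, and on the algorithm attributing one day after removal. It concerns one of three components, so the effect on the primary composite is slight. The CLABSI secondary outcome and its comparison with surveillance rates are affected most. The rule is the same in both arms, and no directional bias is shown. This is a cheap improvement and does not threaten the primary conclusion.

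**What to change.** In Participant timeline {13}, replace the two exceptions with one post-removal culture window equal to the attribution window of the CLABSI algorithm in Additional file 1 (for example, through the calendar day after removal, if the algorithm says so). Apply it to every blood culture drawn in the ICU/HAU, including those on the last unit day, and follow each result until it is available.

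The cost is one sentence in the protocol, matching guidance for the case report form, and about one extra day of culture review per patient. Coordinators already check these patients' imaging reports after line removal.

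One side effect should be recorded. Post-removal events would enter the numerator while catheter days stay as defined, so the expected rate becomes h × (d + r) / d, which depends slightly on dwell. With illustrative values r = 0.45 and d = 5 in control against 6 under EDTA, a true rate ratio of 1 becomes (6.45/6) / (5.45/5) = 1.075 / 1.09 = 0.986. That is small, but a reason to report catheter days by arm alongside the CLABSI rate.

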### Sample size {14}

The results from a 1-month observational study conducted at Royal Columbian Hospital indicate a 20% baseline risk of the composite outcome [32]. The analysis included central venous catheters, PICC lines, and hemodialysis catheters. In previous clinical studies, 4% EDTA solution has shown a 40–70% reduction in occlusion (measured by total alteplase use before vs. after intervention). Assuming a conservative 30% relative risk reduction in the risk of the composite outcome, our sample size calculation is based on an absolute risk reduction from 20 to 14%. A total of 1690 patients need to be recruited to achieve adequate power.

The simulated sample size calculations were performed using R with 10,000 simulation runs, which yields a standard error of 0.4% in the estimated power. The calculation assumed a standard deviation of baseline risk across different ICUs to be 0.02, which corresponded to a within-cluster within-period correlation of 0.0029. The standard deviation between cluster time periods was assumed to be 0.001. A generalized linear mixed effect model was used to generate and analyze the data. The statistical significance was determined using a *t*-test with degrees of freedom equal to the number of cluster periods minus the number of periods minus one [33].

### Recruitment {15}

The results of the observational study conducted at Royal Columbian Hospital’s 30-bed ICU and step-down unit in December 2020 reveal that 75 patients out of a total of 90 met the inclusion criteria to be enrolled in the study. Conservatively, we aim to recruit at least 50 patients per unit per month at each participating unit. We do not perceive recruitment challenges as we have obtained waived consent from relevant ethics boards.

With a three-and-a-half-month enrollment window during each period, each site is expected to recruit at least 175 patients per period. As five ICUs will be participating in this study and each site enrolls for two periods, the enrollment will be 1750 patients in total. Protocol adherence will be deemed a success if there is greater than 85% of patients who are adherent to the entire study protocol.

### Assignment of interventions: allocation

#### Sequence generation {16a}

Randomization involves only the allocation of the five ICUs to the locking solution that will be used during the first period. The randomization will be performed by a statistician at the Centre for Health Evaluation and Outcome Services (CHEOS).

#### Concealment mechanism {16b}

The statistician performing the randomization will disclose the allocations to only the study project manager (PM). The PM will then liaise with each site pharmacy to inform them of their experimental condition so that they can prepare the appropriate locking kits during each period. Blinding of clinicians and research staff will remain throughout the entirety of the trial.

#### Implementation {16c}

Allocation sequence will be generated by the external statistician. Study participants will be enrolled by designated research coordinators at each site. All patients at each participating site will receive the treatment which is being administered at the site during that period.

### Assignment of interventions: blinding

#### Who will be blinded {17a}

Trial participants, care providers, outcome assessors, and data analysts will be blinded to the assignment of intervention. The only research personnel who will be unblinded are the statistician performing the randomization, the PM, and the research pharmacists in charge of supplying locking kits used during the study. As each of the 4% tetrasodium EDTA, saline, and citrate will be placed in 10mL syringes, they will not be distinguishable to the trial participants, care providers, or outcome assessors to maintain their blinding. Data analysis will occur outside of the unit with the type of intervention received by each patient concealed until the completion of analysis.

#### Procedure for unblinding if needed {17b}

If unblinding is necessary for patient management (e.g., in the case of an adverse event (AE) for which patient management requires knowledge of treatment assignment), the investigator will be able to obtain this information by getting approval from the study principal investigator (PI) to contact a designated individual with access to the allocation list. The study PI and the designated individual will be available 24 h per day and 7 days per week. Treatment codes will not be broken except in emergency situations that affect clinical care decisions. The investigator requesting unblinding will document and provide an explanation for the request.

### Data collection and management

#### Plans for assessment and collection of outcomes {18a}

All information collected for each patient will be obtained either by reviewing patient charts or engaging in conversations with the treating nurses daily. Members of the research team at each site will extract each participant’s study data from the patient charts and/or resulting nursing conversations and enter the data directly into a secure, electronic database. The lead investigator will instruct each of the study sites regarding data capture procedures on electronic and/or paper CRFs.

#### Plans to promote participant retention and complete follow-up {18b}

All experimental procedures will be administered by ICU/HAU and the research staff during the patient stay. As such, there will be no efforts to promote participant retention.

Patients will be followed by the members of the research team until they leave the ICU/HAU, they reach the end of the follow-up period, or they die. After leaving the ICU/HAU, the patients will no longer be part of the study and will not be retained. Patients who are transferred out of the ICU/HAU with a central line in situ will no longer receive the study locking solution and revert to the standard of care for the unit to which they have been transferred to. To avoid logistical complications due to the sheer number of participants, patients who leave the ICU/HAU for another hospital unit with their original CVAD still inserted will not be followed. Patients will not be followed past the end of the experimental period.

